### Sample size

The target sample size is 400 patient participants (200 per arm). This will comprise 40 patient participants’ in 10 different sites. As this is a feasibility study, this sample size was not decided on the basis of efficacy analyses; rather this is a purposive selection of groups with relevant experience of hip fracture and confusion and ability to access in the time available. Their data will be used to estimate the intra-class correlation coefficient for each outcome measure. Assuming a coefficient of no more than 0.1, 400 participants from 10 centres should provide a standard error no greater than 0.041, providing a basis for a definitive trial sample size.

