### Setting

The study will be conducted in acute hospital wards in ten NHS hospitals located in five different UK regions (England: four regions, eight hospitals; Scotland: one region, two hospitals) to which individuals who sustain proximal hip fracture are admitted. Each hospital will contribute one study ward. The unit of randomisation is the cluster, in this case, the hospital site. The following site inclusion and exclusion criteria have been identified.

Site inclusion criteria:Sites have an average monthly admission of at least 12 individuals who sustain proximal hip fracture requiring an operation and have a preoperative Abbreviated Mental Test Score (AMTS) ≤8 (England) or a 4AT ≥1 (Scotland) in the last 12 available calendar monthsSites are able to provide the PERFECTED trial team with contextual ward level data (comprising BPT scores, number of falls, pressure ulcers, deaths and safeguarding incidents) in the last 12 available calendar months

Site exclusion criteria: sites that have participated in the “PERFECTED WP2: Implementing optimised hospital care” research programme leading to the development and refinement of PERFECT-ER will be excluded.

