## Analysis

### Quantitative analysis

Data from the trial will be analysed and reported in accordance with Consolidated Standards of Reporting Trials (CONSORT) [23]. An initial estimate of intervention efficacy will be provided using a multi-level model, with hospital as the highest “cluster” level and an appropriate error term depending on the nature of the outcome of interest. Between-treatment-arm effects will be estimated with 95% confidence intervals. Analyses will be on an intention-to-treat basis. There are no plans for imputing missing data and thus analyses will be on a complete-case basis only. No subgroup analyses are planned. In the light of new information, should it be decided during the course of the trial that a subgroup analysis is appropriate, this will be recorded in the statistical analysis plan prior to any data analyses. There will be no formal interim analysis. Deaths, falls, pressure ulcers, admissions to long-term residential care and safeguarding incidents are expected in this patient population. These rates will be collected at ward level throughout the study period. Analysis of recruitment rates, patient participant (including mortality) and suitable informant withdrawal rates will also be reviewed. Based on the data collected from this study, a formal sample size calculation will be carried out to inform a future, definitive trial.

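### The stated ICC standard error of 0.041 does not follow from 10 hospitals of 40 patients at an ICC of 0.1; the standard formula gives about 0.053

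*Protocol article*

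**What the plan says.** The Sample size section of the protocol article sets a target of 400 patients and gives the layout: "This will comprise 40 patient participants’ in 10 different sites". It explains that the number was not derived from efficacy analyses but from a purposive choice of groups and from what could be reached in the time available. It then says that the data will be used to estimate the ICC of each outcome measure, and makes one numerical claim about precision: "Assuming a coefficient of no more than 0.1, 400 participants from 10 centres should provide a standard error no greater than 0.041". This is offered as a basis for sizing a definitive trial.

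Two other places fix what the cluster is. Under Setting: "The unit of randomisation is the cluster, in this case, the hospital site". Under Quantitative analysis, the multi-level model is described "with hospital as the highest “cluster” level". Estimating ICCs for a later sample size is a listed objective (Aims and objectives), and Quantitative analysis adds: "Based on the data collected from this study, a formal sample size calculation will be carried out to inform a future, definitive trial". The article shows no formula or working for the 0.041.

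**The concern.** The precision of an ICC estimate depends mainly on the number of clusters, and ten is few. A standard error of 0.041 at an ICC of 0.1 looks too small for ten hospitals, even with 40 patients in each. The sentence is worded as an upper bound, so it has to hold at the largest ICC it allows, which is 0.1.

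At stake is whether this feasibility trial can deliver what it says about one of its own objectives. The figure is the only quantitative support for the layout of 10 hospitals by 40 patients. If it is too small, readers and those planning the definitive trial are told to expect a more precise ICC than the design can provide, and the error is in the optimistic direction.

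**Working it through.** **Inputs, all from the protocol article.** Number of clusters k = 10 and cluster size m = 40 (Sample size); cluster = hospital (Setting; Quantitative analysis); ICC r = 0.1 as the worst case, and stated standard error 0.041 (Sample size).

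**Formula.** Large-sample standard error of the one-way ANOVA estimator of the ICC:

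SE = (1 − r) × [1 + (m − 1)r] × √{2 / [m(m − 1)(k − 1)]}

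**Attempt to reproduce the plan's figure with the planned layout.** With m = 40, k = 10, r = 0.1:

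- 1 − r = 0.9
- 1 + 39 × 0.1 = 4.9
- 2 / (40 × 39 × 9) = 2 / 14,040, with square root 0.01194
- SE = 0.9 × 4.9 × 0.01194 = **0.0526**

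The stated 0.041 is not reproduced. The ratio is 0.0526 / 0.041 = 1.28.

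**Does another reasonable method give 0.041?** All of these are for 10 hospitals of 40 at r = 0.1.

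| Method | SE |
|---|---|
| Standard formula, divisor k − 1 = 9 | 0.0526 |
| Swiger form | 0.0526 |
| Divisor k = 10 (most lenient) | 0.0499 |
| Divisor k − 2 = 8 (arm effect fitted) | 0.0558 |
| Simulated ANOVA estimator, 9 between-hospital df (1,000,000 draws) | 0.051 |
| Simulated ANOVA estimator, 8 df (arm fitted) | 0.053 |
| Simulated maximum-likelihood estimator, 9 df / 8 df | 0.047 / 0.045 |

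None comes down to 0.041. The maximum-likelihood values are the smallest, but that estimator is biased downwards here: its mean is 0.087 with 9 df and 0.076 with 8 df, against a true value of 0.1.

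**Does the upper-bound wording rescue it?** With k = 10 and m = 40 the standard formula gives:

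| r | SE |
|---|---|
| 0 | 0.012 |
| 0.05 | 0.033 |
| 0.069 | 0.041 |
| 0.07 | 0.0414 |
| 0.10 | 0.0526 |

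The standard error increases with r over this range, so 0.1 is the case that the bound must cover. An SE of 0.041 corresponds to r of about 0.069 (about 0.075 with the lenient divisor k).

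**What layout does give 0.041?** Exchange the two inputs, so that m = 10 and k = 40:

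- 1 + 9 × 0.1 = 1.9
- 2 / (10 × 9 × 39) = 2 / 3,510, with square root 0.02387
- SE = 0.9 × 1.9 × 0.02387 = **0.0408**, which rounds to the printed 0.041

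That layout also totals 400 patients. Sixteen clusters of 40 would give 0.0408 as well, but that is 640 patients and matches nothing in the article.

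**The case against.** The best defence is that little hangs on the number. This is a feasibility trial with no primary outcome. The size of 400 is explained on pragmatic grounds, and the precision sentence describes what that number should yield rather than deriving it. The definitive trial is to be sized from the data collected, so the uncertainty that matters then will be the one estimated from those data. Nothing says that 0.041 will be carried forward, and correcting it changes no patient number, site number or analysis. All of this stands. It limits the consequence; it does not make the figure right. The article chose to state a numerical bound, and its own inputs contradict it, so this is not a detail that could have been left to an analysis plan.

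A reader might infer more than the document supports:

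- *That the whole sample-size justification collapses.* It does not. The pragmatic rationale is untouched; only the quantitative part is wrong.
- *That cluster number and cluster size were certainly swapped.* The match is close and the total agrees, but no working is shown, so this remains an inference.
- *That ten hospitals could never reach 0.041 at an ICC of 0.1.* As m grows without limit, the formula tends to √(2 × 0.81 × 0.01 / 9) = 0.0424 with divisor k − 1, but to 0.0402 with divisor k, and the simulated limit is about 0.041. The claim depends on the form chosen, and the point does not need it.
- *That the correction can be expressed as a symmetric 95% interval, or a design effect built on one.* With 9 between-hospital degrees of freedom the normal approximation is poor: an F-based 95% interval for an estimate of 0.1 runs from about 0.04 to 0.30.
- *That attrition makes it worse by a known amount.* Losses under a complete-case analysis would raise the standard error, but the article gives no attrition figure and the stated bound is for the full 400.

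**Conclusion.** The statement is wrong as written. For the planned 10 hospitals of 40 patients at an ICC of 0.1, the standard error of the ICC is about 0.053, not at most 0.041. The excess is about 28% on the standard formula, and 22% to 36% across its variants (0.0499 / 0.041 = 1.22; 0.0558 / 0.041 = 1.36). The stated bound is true only for ICCs up to about 0.07.

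This rests on equal clusters of 40, the hospital as the only cluster level, a continuous outcome under the usual one-way model and no losses. All but the model are the article's own terms. The conclusion does not depend on how the error arose, and it does not show that 400 patients are too few for a feasibility trial.

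**What to change.** Correct the precision sentence under Sample size in one of two ways:

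1. Keep the ICC assumption of no more than 0.1 and restate the standard error as about 0.053 for 10 centres of 40 patients.
2. Keep 0.041 and limit the assumed ICC to no more than about 0.07.

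In either case, name the formula used so that the figure can be checked. If 0.041 came from a different method or cluster structure, state that method instead. The cost is one sentence and a less favourable precision figure. No change to the number of patients, hospitals or analyses is needed.

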## Analysis

### Quantitative analysis

Data from the trial will be analysed and reported in accordance with Consolidated Standards of Reporting Trials (CONSORT) [23]. An initial estimate of intervention efficacy will be provided using a multi-level model, with hospital as the highest “cluster” level and an appropriate error term depending on the nature of the outcome of interest. Between-treatment-arm effects will be estimated with 95% confidence intervals. Analyses will be on an intention-to-treat basis. There are no plans for imputing missing data and thus analyses will be on a complete-case basis only. No subgroup analyses are planned. In the light of new information, should it be decided during the course of the trial that a subgroup analysis is appropriate, this will be recorded in the statistical analysis plan prior to any data analyses. There will be no formal interim analysis. Deaths, falls, pressure ulcers, admissions to long-term residential care and safeguarding incidents are expected in this patient population. These rates will be collected at ward level throughout the study period. Analysis of recruitment rates, patient participant (including mortality) and suitable informant withdrawal rates will also be reviewed. Based on the data collected from this study, a formal sample size calculation will be carried out to inform a future, definitive trial.

Health and social care costs will be calculated drawing on the trial data, attaching unit costs from published sources to quantities of service use [31, 32]. The additional resource use associated with the intervention will be examined over the period of the trial by tracking potential indicators of impact, such as patient time spent in the anaesthetic room (i.e. this could change because relatives are encouraged to stay with the patient as part of the enhanced recovery checklist). SIL salary costs, on-costs and overheads will be estimated in order calculate their contribution to the costs of participants’ index hospital stays. Cost-effectiveness analyses will be from two perspectives - health and social care and societal. We will analyse outcomes including Bristol Activities for Daily Living Scale (BADLS) (patients) and quality-adjusted life-year (QALY) gain (for patients and carers). Incremental cost-effectiveness ratios will be computed and cost-effectiveness acceptability curves generated to examine the probability of cost-effectiveness over a range of willingness-to-pay thresholds for each outcome. Multivariate analyses of costs and outcomes appropriate for the clustered-randomised trial design will control for centre, baseline outcome measures or costs, and other confounders. We will compare results of analyses using societal, patient and carer weights for QALYs generated from DEMQOL-proxy, and different approaches to valuing unpaid care [32]. Variations in hospital service use within and between patients (e.g. hospital admissions, Accident and Emergency visits) will be explored through latent growth modelling. A sample of Participant Information Sheets and Consent Forms can be found in Additional file 3.

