## Abstract

**Background:**

Health and social care provision for an ageing population is a global priority. Provision for those with dementia and hip fracture has specific and growing importance. Older people who break their hip are recognised as exceptionally vulnerable to experiencing confusion (including but not exclusively, dementia and/or delirium and/or cognitive impairment(s)) before, during or after acute admissions. Older people experiencing hip fracture and confusion risk serious complications, linked to delayed recovery and higher mortality post-operatively. Specific care pathways acknowledging the differences in patient presentation and care needs are proposed to improve clinical and process outcomes.

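### Not imputing does not require complete-case analysis: the rule, read literally, discards observed follow-up data and could remove patients who die from QALYs and costs

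*Protocol article*

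**What the plan says.** All quotes are from the Quantitative analysis section of the protocol article unless stated otherwise.

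- Model: "An initial estimate of intervention efficacy will be provided using a multi-level model, with hospital as the highest “cluster” level". The section does not say whether this means one model per visit or one repeated-measures model.
- Estimates: "Between-treatment-arm effects will be estimated with 95% confidence intervals".
- Population: "Analyses will be on an intention-to-treat basis".
- Missing data, in the next sentence: "There are no plans for imputing missing data and thus analyses will be on a complete-case basis only". No exception and no sensitivity analysis is named.
- Deaths: "Deaths, falls, pressure ulcers, admissions to long-term residential care and safeguarding incidents are expected in this patient population". The rates of these events are collected at ward level. The Abstract adds: "Older people experiencing hip fracture and confusion risk serious complications, linked to delayed recovery and higher mortality post-operatively".
- Attrition: "patient participant (including mortality) and suitable informant withdrawal rates will also be reviewed".
- Economic outcomes include "quality-adjusted life-year (QALY) gain (for patients and carers", with cost-effectiveness ratios and acceptability curves. How a patient's death enters the QALY or the cost is not stated.

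Aims and objectives asks for efficacy estimates at 1, 3 and 6 months, intra-class correlations, and estimates of retention and completeness. The Discussion foresees difficulty in finding informants and in keeping them through follow-up.

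**The concern.** The word 'thus' in the missing-data sentence turns a decision not to impute into a decision to analyse complete cases only. These are separate decisions. A multilevel model fitted by likelihood to visits within patients within hospitals takes whatever values exist and fills in none. A patient seen at 1 and 3 months but not at 6 then contributes both observed values, and they also inform the 6-month estimate.

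This is a stated rule rather than a detail left open, so an analysis plan that complies with the protocol would inherit it. It is set for patients among whom the protocol itself expects deaths, and it depends on informants whom the protocol expects to be hard to keep.

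Three outputs for the definitive trial are at stake:

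- **Effect estimates at later visits.** A 6-month complete-case comparison ignores what earlier visits show about patients who were later lost.
- **Patient QALYs and costs.** These accumulate over the whole follow-up, so one missed visit can make a patient incomplete. A patient who dies has no 6-month score, and nothing in the text says that such a patient is to be kept.
- **Retention.** Death and avoidable loss have different implications for planning, so the two are needed separately.

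**Working it through.** The plan gives no figure for deaths, missed visits or complete cases, so there is none to reproduce. The step that can be checked is the inference; the arithmetic after it illustrates scale on assumed rates.

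**1. The inference.** Premise: nothing is imputed. Conclusion: complete cases only. The counter-example is a likelihood-based multilevel model with visit, arm and arm-by-visit terms. It satisfies the premise without the conclusion and is valid if missingness depends on observed data. A separate 6-month complete-case model needs the stricter condition that missingness does not depend on the 1- and 3-month scores, given what is in the model. The protocol already plans multilevel models, and latent growth modelling for service use, so the method is within the team's reach.

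**2. Patients retained.** From the document: 400 patients (Sample size) and follow-up at 1, 3 and 6 months (Data collection). Assumed: a proportion d dies by 6 months, and each survivor misses any one visit with probability v, independently between visits.

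- With a 6-month value: 400 × (1 − d) × (1 − v)
- With all three follow-ups: 400 × (1 − d) × (1 − v)³
- Survivors with at least one follow-up: 400 × (1 − d) × (1 − v³)

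| d (v = 0.10) | Survivors | 6-month value | All three | At least one |
|---|---|---|---|---|
| 0.10 | 360 | 324 | 262 | 360 |
| 0.20 | 320 | 288 | 233 | 320 |
| 0.30 | 280 | 252 | 204 | 280 |

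At d = 0.20, requiring all three visits leaves out about 320 − 233 = 87 survivors who have some follow-up data, and also anyone who was assessed and then died. With v from 0.05 to 0.15 and d from 0.10 to 0.30, the all-visit count runs from 309 (400 × 0.90 × 0.95³) down to 172 (400 × 0.70 × 0.85³), or 77% to 43% of 400.

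**3. Patient QALYs, if patients who die were removed.** Assumed: utility u = 0.4 while alive, 0.5 years of follow-up, and deaths spread evenly, so that a patient who dies lives 0.25 years on average.

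- Survivors only: 0.4 × 0.5 = 0.200
- All patients: 0.4 × [0.5 × (1 − d) + 0.25 × d]
- d = 0.20: 0.4 × (0.400 + 0.050) = 0.180
- d = 0.25: 0.4 × (0.375 + 0.0625) = 0.175
- d = 0.30: 0.4 × (0.350 + 0.075) = 0.170

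If mortality were 25% in one arm and 20% in the other, with equal utility among survivors, the all-patient difference would be 0.180 − 0.175 = 0.005 QALY. A survivor-only analysis would give 0.

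**4. Intra-class correlation.** The large-sample standard error is (1 − r)(1 + (m − 1)r) × √[2 / (m(m − 1)(k − 1))], with r = 0.1 and k = 10 hospitals.

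- m = 40: 0.9 × 4.9 × √(2/14040) = 0.0526
- m = 28: 0.9 × 3.7 × √(2/6804) = 0.0571
- m = 24: 0.9 × 3.3 × √(2/4968) = 0.0596

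Losing 12 to 16 of 40 patients per hospital therefore costs little precision, because the number of hospitals dominates. This formula does not return the 0.041 given under Sample size. That is a separate matter, and nothing here rests on it.

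**The case against.** Several stronger readings are tempting, and the document does not support them.

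- **That QALYs will be estimated in survivors only.** A reader might infer this, but the economic paragraph does not say how death is handled. Zero utility after death is a known value, not an imputed one, so it can coexist with the rule. QALY construction is also commonly left to an analysis plan, and that plan is not shown. What stands is that nothing exempts patients who die from a rule worded as applying to all analyses.
- **That anyone who misses a visit is dropped.** With one model per visit, a patient absent at 3 months still counts at 1 and 6 months. The claim fits only outcomes built from all visits.
- **That death is treated as dropout.** Mortality is named within the review of withdrawal rates, but the text does not say that a single pooled figure will be reported. The separate death rates are ward-level and do not replace participant deaths by arm, so asking for those is a fair clarification.
- **That the rule contradicts intention to treat.** Patients can be analysed in their randomised arm and still be limited to those with outcomes. The two sentences are in tension, but they are not strictly contradictory.

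The consequences are also limited. The trial has no primary outcome, efficacy is only an initial estimate, and completeness is itself an objective. Hospital use comes from clinical records as well as from informants. The illustrated QALY difference is small and wholly assumed.

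A mixed model is not a complete remedy either. It implicitly extrapolates scores past death, so its estimates need a stated interpretation.

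**Conclusion.** The complete-case-only rule rests on a step that does not follow. Read literally, it discards observed follow-up data in a population where the protocol expects deaths and lost contact. QALYs and costs are most exposed, and patients who die could be removed from them because the text makes no exception. Whether they would be is not stated.

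The size of the loss or bias cannot be computed from the document. The counts of 324 to 252 (6-month value) and 262 to 204 (all visits), and the 0.005 QALY, rest on assumed mortality, missed visits, utility and timing of death. They show scale only.

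This should be fixed as a cheap improvement. It does not threaten the trial: this is a feasibility study without a primary outcome, and the effect on the precision of the intra-class correlation is small.

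**What to change.** Replace the complete-case sentence with three statements.

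1. Repeated outcomes are analysed without imputation in a likelihood-based multilevel model (visits within patient within hospital, with arm-by-time terms) using all available 1-, 3- and 6-month values. Scores after death are treated as undefined. The estimates are described either as conditional on being alive or as resting on the model's assumption about death.
2. In patient QALYs and patient costs, those who die are retained, with zero utility and zero further cost from death. The date of death is used or, if it is not recorded, the visit interval in which death occurred. Carer QALYs are not set to zero when the patient dies.
3. Participant deaths are reported by arm, separately from withdrawal and from loss to follow-up.

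The cost is slightly more analysis work and reliance on a missing-at-random assumption for missingness not due to death. The visible text does not confirm that dates of death are collected (the assessment figure is not shown), which is why item 2 has a fallback. The change is best made before any analysis.
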